### Data collection and quality control

4.4

Intervention staff will comprise public health physicians certified in nutrition, and sample collection will be performed by registered nurses with clinical laboratory experience. All personnel will complete standardized training prior to conducting enrollment, follow-up assessments, and biospecimen collection. Instruments and reagents will be calibrated and quality-controlled per SOPs at baseline and at scheduled intervals.

## Study outcomes

5

### Time window for outcome measurement

5.1

Outcome assessments will be conducted at baseline (Week 0) and at Weeks 4, 8, and 12. Physical examinations and questionnaire surveys will be completed at each visit. Additionally, serum, urine, and stool samples will be collected for biochemical and multi-omics analyses, enabling longitudinal assessment across pre-, mid-, and post-intervention phases. At each study site, sampling materials will be distributed prior to the Week 4, 8, and 12 visits. Participants will be reminded to fast overnight and to bring first-morning urine and stool samples. On the visit day, physical measurements, blood sampling, and questionnaire administration will be completed. Biospecimens will then be transported under cold-chain conditions to Peking University for subsequent analysis. The time window for outcome measurement is presented in Table 4.

**Table 4 T4:** Time window for outcome measurement.

Outcome		Time point				Sample collection/Method
		Baseline	4 weeks	8 weeks	12 weeks	
**Omega-3 PUFA biological marker**		√	√	√	√	Blood samples
**Glucose metabolism-related parameters**		√	√	√	√	
**Lipid metabolism-related parameters**		√	√	√	√	
**Metabolomics**		√	√	√	√	Blood, urine, and stool samples
**Intestinal flora**		√	√	√	√	Stool samples
**Questionnaire survey**	**Food intake**	√	√	√	√	Food frequency questionnaire (FFQ)/3-day 24-h dietary record
	**Physical activity**	√	√	√	√	International physical activity questionnaire short form (IPAQ-SF)
	**Sleep quality**	√	√	√	√	Pittsburgh sleep quality index (PSQI)
	**Mood state scale**	√	√	√	√	Profile of mood states (POMS)
	**Cognitive scale**	√	√	√	√	Montreal cognitive assessment (MoCA)
**Physical measurements**		√	√	√	√	Stadiometer, weight scale, flexible measuring rule, bioelectrical impedance analyzer

### Plasma omega-3 PUFA as biomarkers

5.2

In this study, plasma omega-3 PUFAs will serve as objective biomarkers of intervention exposure, reflecting changes in participants' omega-3 intake and absorption, and enabling assessment of their relationship with metabolic outcomes. Samples will be collected at baseline (Week 0) and at Weeks 4, 8, and 12 of the intervention, coinciding with primary follow-up visits. Fasting venous blood samples will be collected, and plasma will be separated and stored at −80 C until analysis. Plasma concentrations of DHA, EPA and ALA will be quantified. Results will be expressed as absolute concentrations and, if necessary, as percentages of total fatty acids to facilitate inter-individual comparisons (22). Total lipids will be extracted from plasma using standardized procedures and quantified by gas chromatography (GC-FID or GC-MS) or liquid chromatography-tandem mass spectrometry (LC-MS/MS). Internal standards and quality control samples will be included in each assay batch to ensure consistency (23). These measurements will validate enhanced *in vivo* omega-3 exposure in the omega-3 PUFA-enriched egg group relative to the standard egg group, supporting subsequent pathway analyses of the “omega-3 exposure (DHA/EPA/ALA changes)–metabolic phenotype (e.g., TG)–omics signatures” relationship (24, 25).

### Primary outcome

5.3

The primary outcome will be defined as the longitudinal trajectory of fasting triglycerides (TG) measured at Weeks 0, 4, 8, and 12. The primary statistical analysis will focus on the group × time interaction, indicating differences in TG trends over time among intervention groups. The pre-specified primary comparison will be between the omega-3 PUFA-enriched egg group and the standard egg group to evaluate intervention efficacy. Exploratory pairwise comparisons will also be conducted for other group combinations not specified in the primary hypothesis.

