**Results:**

The primary outcome will be the longitudinal changes in fasting triglycerides (TG) measured at Weeks 0, 4, 8, and 12, with comparisons between the omega-3 PUFA-enriched eggs group and the regular eggs control group. Secondary outcomes will include glucose levels, insulin concentrations, lipid profiles, as well as biomarkers of inflammation and oxidative stress. Integrative multi-omics analyses will be conducted to explore the pathways linking omega-3 PUFA-enriched eggs consumption to alterations in metabolomic features and gut microbiota.

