### Sample size calculation

2.3

This three-arm randomized controlled trial will adopt an allocation ratio of 1:1:1. The primary outcome will be the change in fasting serum triglyceride (TG) levels from baseline to the end of the intervention. The main effect to be tested will be the difference in TG level changes between the omega-3 PUFA-enriched eggs intervention group and the regular eggs group. Based on previous dietary intervention studies in populations with metabolic syndrome, the estimated standard deviation of fasting serum TG is approximately 58 mg/dL (baseline TG level: 140.9 ± 58.0 mg/dL) (19). Sample size estimation will be based on data from a prior randomized trial, which reported a 35 mg/dL difference in triglyceride (TG) levels between participants consuming omega-3 PUFA-enriched eggs (152.476 mg/dL) and those consuming regular eggs (187.333 mg/dL) (20). Accordingly, the minimal clinically meaningful difference (δ) will be set at 35 mg/dL. Assuming a two-sided significance level of 0.05 and 80% statistical power (1–β = 0.80), the required sample size will be computed using the standard formula for comparing means between independent groups:

$$\begin{array}{l} N=\frac{2{\left(Z_{1-\frac{\alpha }{2}}+Z_{1-\beta }\right)}^{2}}{\delta^{2}} \end{array}$$

Where Z_1−α/2_ = 1.96, Z_1−β_ = 0.84, σ = 58 mg/dL, and δ = 35 mg/dL. Consequently, to meet the statistical power requirements for the primary comparison, approximately 44 participants per group will be needed. Considering a potential dropout rate of approximately 25% in 12-week dietary intervention studies among elderly populations (21), the sample size will increase accordingly:

$$\begin{array}{l} n=\frac{44}{1-0.25}\approx 59 \end{array}$$

Therefore, the final target sample size will be set at 60 participants per group, yielding a total of 180 participants across the three arms.

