### Key secondary outcomes and exploratory outcomes

5.4

Blood samples will be collected at baseline (Week 0) and Weeks 4, 8, and 12 to assess indicators related to glucose and lipid metabolism (four samples per participant, covering lipid profiles, glucose homeostasis, inflammatory markers, oxidative stress, and other metabolic parameters). Samples will be collected following an overnight fast, with serum and plasma separated according to standardized protocols. Aliquots will be stored at −80 C and shipped in batches for centralized analysis. Biochemical and immunological markers will be quantified using enzyme-linked immunosorbent assay (ELISA) and other validated methods, with rigorous technical support to ensure intra- and inter-assay consistency and full traceability.

Key secondary outcomes:

(1) Lipid metabolism indicators included total cholesterol (TC), triglycerides (TG), high-density lipoprotein cholesterol (HDL-C), low-density lipoprotein cholesterol (LDL-C), free fatty acids (FFA), lipoprotein(a) [Lp(a)], apolipoprotein A1 (ApoA1), and apolipoprotein B (ApoB). These indicators will provide a comprehensive assessment of lipid metabolism disorders and associated cardiovascular risk.(2) Inflammation and oxidative stress markers: Measured indicators will include high-sensitivity C-reactive protein (hs-CRP), interleukin-1 (IL-1), interleukin-6 (IL-6), tumor necrosis factor-alpha (TNF-α), and oxidative stress markers such as superoxide dismutase (SOD) and glutathione (GSH).

Exploratory outcomes:

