(1) Glucose metabolism and insulin resistance indicators: Measured markers will include fasting plasma glucose (FPG), glycated hemoglobin (HbA1c), fasting insulin, and C-peptide to assess glycemic control and pancreatic β-cell function. Additionally, the homeostasis model assessment of insulin resistance (HOMA-IR) will be calculated as: HOMA-IR = [FPG (mmol/L) × FINS (mU/L)] ÷ 22.5, where higher values indicate greater insulin resistance.(2) Metabolomics: This study will employ untargeted metabolomics to characterize the systemic effects of omega-3 PUFA-enriched egg intervention on metabolic phenotypes, aiming to identify potential metabolic pathways and biomarkers associated with primary clinical outcomes. Plasma, urine, and stool samples will be collected at baseline (Week 0) and follow-up visits (Weeks 4, 8, and 12), then stored at −80 C pending analysis. Metabolite features will be detected using liquid chromatography-mass spectrometry (LC-MS). To ensure reproducibility, standardized protocols adhering to the Minimum Reporting Standards for Metabolomics and Chemical Analysis Reporting Elements will be implemented throughout sample preparation, instrument operation, metabolite annotation, identification, and data preprocessing (26). Additionally, quality control samples will be incorporated to monitor analytical drift and batch effects, with corrections applied as needed to enhance data quality and comparability (27). Metabolomic results will provide exploratory mechanistic insights, which will be interpreted in conjunction with clinical phenotypes and findings from other omics analyses.(3) Gut microbiomics: Gut microbiota-related indicators will be evaluated as exploratory mechanistic outcomes to elucidate potential gut-derived mechanisms underlying metabolic phenotype changes (e.g., triglycerides) in older adults with metabolic syndrome following omega-3 PUFA-enriched egg intervention. Primary microbiome measures will include α-diversity, β-diversity, community structure comparisons, and analyses of differential microbial abundance and functional pathways.

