Stool samples will be collected at baseline (Week 0) and at Weeks 4, 8, and 12, and then stored at−80 C for subsequent analysis. The primary analytical endpoint will align with the clinical outcomes (Week 12), while samples collected at Weeks 4 and 8 will be analyzed to explore temporal changes and potential mechanisms. To ensure reproducibility and comparability, all procedures—including sample collection, storage, DNA extraction, sequencing, and statistical analyses—will follow standard operating procedures and reporting guidelines for human stool sample processing (28, 29).

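### The primary triglyceride outcome is defined in two ways, and the stated 80% power belongs to the end-of-intervention two-arm difference, not to the group × time interaction named as the primary analysis

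*Protocol article*

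**What the plan says.** Section 2.3 (Sample size calculation) gives one definition: "The primary outcome will be the change in fasting serum triglyceride (TG) levels from baseline to the end of the intervention". Regular eggs are the comparator, and the quantity tested is the two-arm difference in that change ("The main effect to be tested will be the difference in TG level changes between the omega-3 PUFA-enriched eggs intervention group"). It is sized with a two-sample formula for means, using a difference of 35 mg/dL, SD 58 mg/dL, two-sided 5% and 80% power. The result is 44 per group, raised to 59 for 25% dropout and set at 60.

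Section 5.3 (Primary outcome) gives another: "The primary outcome will be defined as the longitudinal trajectory of fasting triglycerides (TG) measured at Weeks 0, 4, 8, and 12". The abstract follows this version. Section 5.3 then says: "The primary statistical analysis will focus on the group × time interaction, indicating differences in TG trends over time among intervention groups". Its next sentences make enriched versus regular eggs the pre-specified primary comparison and the other pairs exploratory.

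Section 7 (Data entry and analysis) specifies an MMRM with group, time point and group × time, and names no contrast that decides the trial. Section 5.4, writing about the stool samples, places the clinical outcomes at week 12: "The primary analytical endpoint will align with the clinical outcomes (Week 12").

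Two smaller inconsistencies concern the outcome levels. TG, the primary outcome, reappears in the key secondary list of section 5.4 ("Lipid metabolism indicators included total cholesterol (TC), triglycerides (TG"). Glucose and insulin are secondary in the abstract ("Secondary outcomes will include glucose levels, insulin concentrations, lipid profiles") but exploratory in section 5.4 ("Glucose metabolism and insulin resistance indicators").

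**The concern.** The change to the end of the intervention between two arms is a single contrast. It has one degree of freedom, one estimate and one confidence interval to set against 35 mg/dL. The group × time interaction asks whether the mean profiles over four visits are parallel. With time as a factor and week 0 among the visits, that is (2 − 1) × (4 − 1) = 3 degrees of freedom for the two egg arms, or (3 − 1) × (4 − 1) = 6 for all three arms. It responds to a difference in change at any visit and gives no single effect size.

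Naming the pair of arms does not settle which of these decides. Two analysts following different sections could draw opposite primary conclusions from the same data, and a choice made after the data are seen would leave the primary result open to selection. The stated 80% power describes only one of the two tests. A separate analysis plan could not simply fill a gap here; it would have to overrule one of two definitions that the protocol article states.

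**Working it through.** **Inputs from section 2.3.** δ = 35 mg/dL, σ = 58 mg/dL, z-values 1.96 and 0.84, dropout 25%, 60 randomised per group. Evaluable per arm: 60 × 0.75 = 45.

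**Inputs that are assumptions.** The document gives neither the within-person correlation ρ nor the time profile of the effect. I take equal correlation between all visits, ρ = 0.5 (range 0.3 to 0.7), complete data at 45 per arm, and a chi-square approximation.

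**1. The plan's own figure.** n = 2 × (1.96 + 0.84)² × 58² / 35² = 2 × 7.84 × 3364 / 1225 = 43.06, so 44. Then 44 / 0.75 = 58.7, so 59, set at 60. The figures reproduce for a one-degree-of-freedom, two-arm difference in means. (The printed formula lacks σ², but 44 is obtained only with it, so this looks like a typographical slip.)

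**2. Power of the sized contrast.** The SD of a change is 58 × √(2(1 − ρ)), which equals 58 at ρ = 0.5. With 45 per arm, the standard error is 58 × √(2/45) = 12.23, and 35 / 12.23 = 2.86. Power = Φ(2.86 − 1.96) = 82%.

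**3. Two-arm interaction, 3 degrees of freedom.** Let d be the vector of enriched-minus-regular differences in change at weeks 4, 8 and 12. Its noncentrality is λ = (n/2) × d′V⁻¹d, with V = σ²(1 − ρ)(I + J), where J is the 3 × 3 matrix of ones. Because (I + J)⁻¹ = I − J/4, this becomes

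λ = (n/2) × [Σd² − (Σd)²/4] / [σ²(1 − ρ)].

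At ρ = 0.5 the denominator is 3364 × 0.5 = 1682. The 5% critical value is 7.81.

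| Profile of d (weeks 4, 8, 12) | Σd² − (Σd)²/4 | λ | Interaction rejects | Week-12 contrast rejects |
|---|---|---|---|---|
| Linear: 11.7, 23.3, 35 | 1905.6 − 1225 = 680.6 | 9.10 | 72% | 82% |
| From week 4: 35, 35, 35 | 3675 − 2756.25 = 918.75 | 12.29 | 85% | 82% |
| Week 4 only: 35, 0, 0 | 1225 − 306.25 = 918.75 | 12.29 | 85% | 5% (null) |

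The last row shows the conflict: the section 5.3 test usually rejects while the quantity sized in section 2.3 is zero.

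**4. Sensitivity to ρ (two arms, 45 per arm).**

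| ρ | Sized contrast | Interaction, linear | Interaction, from week 4 |
|---|---|---|---|
| 0.3 | 68% | 56% | 70% |
| 0.5 | 82% | 72% | 85% |
| 0.7 | 96% | 92% | 98% |

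At each ρ the interaction's power lies below or above that of the sized contrast according to the time profile. If correlation instead decays between visits (first-order autoregressive, 0.8 between adjacent visits), the sized contrast has 83%, and the interaction 68% for the linear profile and 98% for an effect from week 4.

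**5. Number needed if the two-arm interaction stayed primary.** At ρ = 0.5, 80% power needs 54 evaluable per arm for a linear build-up and 40 for an effect from week 4, against 44 stated.

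**The case against.** The strongest reply is that the document agrees on the comparison. The abstract, section 2.3 and section 5.3 all name enriched versus regular eggs, and section 5.3 makes other pairs exploratory. The MMRM in section 7 already yields the week-12 contrast between those arms, and section 5.4 places the clinical outcomes at week 12. On this view only a clarification is missing. A two-arm interaction test would also be a legitimate primary analysis if the trial were sized for it.

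Much of this stands. The pair of arms is fixed and no new analysis is needed. But no section says which time point or contrast decides, and the week-4-only case in the working is computed for those two arms alone, so naming the pair does not remove the conflict.

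Two stronger readings are tempting and are not supported:

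- **That a difference confined to the blank control arm would count as success.** If enriched equals regular and only blank differs by 35 mg/dL, the three-arm test rejects 74% (linear) to 88% (from week 4) of the time at ρ = 0.5. That follows only if the interaction among all groups is itself the decision rule. It is one literal reading of a single sentence, and the next sentence points to the two egg arms.
- **That the trial is underpowered.** Interaction power can be lower or higher than that of the sized contrast, and the document supplies neither quantity that would settle it.

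**Conclusion.** The point holds as an inconsistency in the definition of the primary outcome. The sizing of 44, 59 and 60 per group is arithmetically sound for the end-of-intervention two-arm difference in change. The primary analysis that section 5.3 describes is a different, multi-degree-of-freedom test to which the stated 80% does not apply.

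The practical size is that a transient week-4 difference of 35 mg/dL would make the two-arm interaction positive about 85% of the time at ρ = 0.5 (70% at 0.3, 98% at 0.7) with no difference at week 12. These figures rest on SD 58, 45 evaluable per arm, equal correlation between visits, time treated as a factor and week 0 counted among the visits. The mismatch itself rests on none of them; it is in the text. It should be corrected before recruitment because it determines what counts as a positive trial. The double listing of TG and the differing level of glucose and insulin are minor labelling matters and do not carry the conclusion.

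**What to change.** State one primary estimand in the same words in the abstract and sections 2.3, 5.3 and 7: the enriched-minus-regular difference in mean fasting TG change from baseline to week 12. Estimate it as the one-degree-of-freedom week-12 contrast from the MMRM, tested at two-sided 5%. Describe the group × time interaction and the trajectory comparisons as supportive. Check that the registry entry agrees; the outcomes row of Table 1 does not say which outcome is primary.

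This keeps N = 180 on the protocol's own SD and makes the stated power belong to the stated test. If the sponsor prefers to keep the interaction as primary, the sample size would have to be recomputed for it, with the correlation and time profile stated.

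As tidying, remove TG from the key secondary list in section 5.4, and give glucose and insulin one level, secondary or exploratory, throughout.

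The cost is wording and, if needed, a registry update. Table 1 gives the recruitment state as not yet recruiting, and no participants, visits or assays are added.

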### Key secondary outcomes and exploratory outcomes

5.4

Blood samples will be collected at baseline (Week 0) and Weeks 4, 8, and 12 to assess indicators related to glucose and lipid metabolism (four samples per participant, covering lipid profiles, glucose homeostasis, inflammatory markers, oxidative stress, and other metabolic parameters). Samples will be collected following an overnight fast, with serum and plasma separated according to standardized protocols. Aliquots will be stored at −80 C and shipped in batches for centralized analysis. Biochemical and immunological markers will be quantified using enzyme-linked immunosorbent assay (ELISA) and other validated methods, with rigorous technical support to ensure intra- and inter-assay consistency and full traceability.

Key secondary outcomes:

(1) Lipid metabolism indicators included total cholesterol (TC), triglycerides (TG), high-density lipoprotein cholesterol (HDL-C), low-density lipoprotein cholesterol (LDL-C), free fatty acids (FFA), lipoprotein(a) [Lp(a)], apolipoprotein A1 (ApoA1), and apolipoprotein B (ApoB). These indicators will provide a comprehensive assessment of lipid metabolism disorders and associated cardiovascular risk.(2) Inflammation and oxidative stress markers: Measured indicators will include high-sensitivity C-reactive protein (hs-CRP), interleukin-1 (IL-1), interleukin-6 (IL-6), tumor necrosis factor-alpha (TNF-α), and oxidative stress markers such as superoxide dismutase (SOD) and glutathione (GSH).

Exploratory outcomes:

(1) Glucose metabolism and insulin resistance indicators: Measured markers will include fasting plasma glucose (FPG), glycated hemoglobin (HbA1c), fasting insulin, and C-peptide to assess glycemic control and pancreatic β-cell function. Additionally, the homeostasis model assessment of insulin resistance (HOMA-IR) will be calculated as: HOMA-IR = [FPG (mmol/L) × FINS (mU/L)] ÷ 22.5, where higher values indicate greater insulin resistance.(2) Metabolomics: This study will employ untargeted metabolomics to characterize the systemic effects of omega-3 PUFA-enriched egg intervention on metabolic phenotypes, aiming to identify potential metabolic pathways and biomarkers associated with primary clinical outcomes. Plasma, urine, and stool samples will be collected at baseline (Week 0) and follow-up visits (Weeks 4, 8, and 12), then stored at −80 C pending analysis. Metabolite features will be detected using liquid chromatography-mass spectrometry (LC-MS). To ensure reproducibility, standardized protocols adhering to the Minimum Reporting Standards for Metabolomics and Chemical Analysis Reporting Elements will be implemented throughout sample preparation, instrument operation, metabolite annotation, identification, and data preprocessing (26). Additionally, quality control samples will be incorporated to monitor analytical drift and batch effects, with corrections applied as needed to enhance data quality and comparability (27). Metabolomic results will provide exploratory mechanistic insights, which will be interpreted in conjunction with clinical phenotypes and findings from other omics analyses.(3) Gut microbiomics: Gut microbiota-related indicators will be evaluated as exploratory mechanistic outcomes to elucidate potential gut-derived mechanisms underlying metabolic phenotype changes (e.g., triglycerides) in older adults with metabolic syndrome following omega-3 PUFA-enriched egg intervention. Primary microbiome measures will include α-diversity, β-diversity, community structure comparisons, and analyses of differential microbial abundance and functional pathways.

Stool samples will be collected at baseline (Week 0) and at Weeks 4, 8, and 12, and then stored at−80 C for subsequent analysis. The primary analytical endpoint will align with the clinical outcomes (Week 12), while samples collected at Weeks 4 and 8 will be analyzed to explore temporal changes and potential mechanisms. To ensure reproducibility and comparability, all procedures—including sample collection, storage, DNA extraction, sequencing, and statistical analyses—will follow standard operating procedures and reporting guidelines for human stool sample processing (28, 29).

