### Study participants

2.4

Participants will be recruited from Guangyang District, Langfang City, Hebei Province, using purposive and convenience sampling methods. Recruitment strategies will include community health clinic screenings, health education sessions, and telephone invitations.

Inclusion Criteria: Community-dwelling adults aged ≥ 65 years with a clinical diagnosis of MetS will be included. MetS will be defined as meeting at least three of the following five criteria: (i) abdominal obesity: waist circumference ≥90 cm (men) or ≥85 cm (women); (ii) hyperglycemia: fasting plasma glucose ≥6.1 mmol/L or 2-h post-load glucose ≥7.8 mmol/L on oral glucose tolerance test (OGTT), or previously diagnosed diabetes currently under treatment; (iii) elevated blood pressure: systolic blood pressure ≥130 mmHg and/or diastolic blood pressure ≥85 mmHg, or previously diagnosed hypertension currently under treatment; (iv) hypertriglyceridemia: fasting triglycerides ≥1.70 mmol/L; and (v) low high-density lipoprotein cholesterol: fasting HDL-C < 1.04 mmol/L.

Exclusion criteria: (i) medical conditions—severe hepatic or renal impairment, immunodeficiency disorders, active infectious diseases, type 1 diabetes, malignant hypertension, malignancy, thyroid dysfunction, electrolyte disturbances, acute diabetic complications or severe chronic complications (including cardiovascular or cerebrovascular events within the preceding month), prior bariatric surgery, or recent significant weight change (>5% over 3 months or >10% over 6 months); (ii) dietary factors—adherence to specialized therapeutic diets or substantial dietary modification within 12 weeks prior to enrollment; (iii) cognitive and functional status—severe medical or psychiatric disorders, or cognitive, visual, or hearing impairments that would preclude study compliance; (iv) medication and supplement use—current use of omega-3 PUFA supplements or medications known to affect lipid metabolism (concomitant medication use will be systematically documented during the screening visit via a comprehensive medication questionnaire); and (v) allergies—documented egg allergy.

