### Intervention initiation and follow-up data collection

3.5

Intervention week 0 (first day of Week 2): During the baseline week, structured questionnaires will be administered to assess dietary intake, psychological status, sleep quality, physical activity, cognitive function, medical history, and concomitant medication and supplement use. Trained physicians will perform standardized anthropometric measurements, including height, weight, waist circumference, blood pressure, and body composition. Participants will be instructed to collect midstream urine samples from the first morning void using clean, sterile disposable containers, which will be transferred to pre-labeled urine collection tubes for storage and subsequent analysis. Fresh stool samples will be self-collected in sterile containers and delivered to research personnel for gut microbiota and metabolomic analyses. Fasting antecubital venous blood samples will also be obtained for outcome assessment. Participants will complete and submit three-day dietary records for verification. They will then receive eggs corresponding to their randomized group allocation, along with a “Participant Diary” for daily recording of egg consumption, supplement use, and medication intake. Diary entries and video documentation of egg consumption will be uploaded to a secure online platform to enable real-time monitoring and compliance verification by research staff. Community physicians will evaluate chronic disease complications and intercurrent symptoms based on physiological parameters, with detailed documentation of onset times, treatments, and durations to facilitate subsequent data analysis.

Intervention Weeks 4, 8, and 12: Follow-up assessments will mirror the Week 0 procedures. Fasting antecubital venous blood samples will be collected by trained medical personnel at each visit.

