## Data entry and analysis

7

**Data entry:** Questionnaire data will be collected directly via electronic forms with built-in logic checks to ensure the accuracy and completeness of data entry, minimizing errors in data recording.

**Statistical analysis:** Statistical analyses will be performed using SPSS 24.0 and R 4.2.0 software. For baseline variables, continuous variables will be analyzed using one-way analysis of variance (ANOVA) or kruskal-wallis tests, while categorical variables will be analyzed using chi-square tests or Fisher's exact tests.

For longitudinal outcome measures, mixed-model repeated measures analysis of variance (MMRM) with an unstructured covariance matrix will be adopted as the primary analytical method. This model will include intervention group, time point, and group × time interaction as fixed effects, with subject-specific random intercepts. Pre-specified covariates (including age, sex, body mass index (BMI), baseline dietary intake, physical activity, baseline clinical parameters, and compliance) will be adjusted in the primary analysis based on their correlation with outcomes and clinical relevance.

Missing data will be handled using intention-to-treat (ITT) analysis with mixed models, which can accommodate unbalanced data under the missing at random (MAR) assumption. Sensitivity analyses will include complete case analysis and multiple imputation by chained equations (MICE) to verify the robustness of the results.

For multi-omics analyses (microbiome and metabolomics), Benjamini-hochberg false discovery rate (FDR) correction (*q* < 0.05) will be applied to control the expected proportion of false positives among the results. Microbiome data will undergo centered log-ratio (CLR) transformation to address compositional data constraints. Non-parametric methods [Friedman test, permutation-based multivariate analysis of variance (MANOVA)] will be used when the assumptions of normality or homogeneity of variance are violated. Principal coordinate analysis (PCoA) based on bray-curtis distances will be used to analyze microbiome composition, and principal component analysis (PCA) will be applied to metabolomics data. Associations between the microbiome and metabolome will be analyzed using sparse partial least squares (sPLS) or canonical correlation analysis (CCA), with FDR correction applied to ensure the reliability of the results.

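### HOMA-IR and fasting insulin are not restricted by treatment, so they do not measure insulin resistance in eligible participants who inject insulin (minor, exploratory outcome)

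*Protocol article*

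**What the plan says.** Section 5.4 of the protocol article, under exploratory outcomes, defines the index as fasting glucose (mmol/L) times fasting insulin (mU/L) divided by 22.5, "where higher values indicate greater insulin resistance". The same paragraph lists "fasting insulin, and C-peptide to assess glycemic control and pancreatic β-cell function". Table 4 schedules the glucose parameters at baseline and at Weeks 4, 8 and 12.

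Section 2.4 allows the hyperglycaemia criterion to be met by "previously diagnosed diabetes currently under treatment". The medical exclusions include "active infectious diseases, type 1 diabetes, malignant hypertension, malignancy, thyroid dysfunction", and no other type of diabetes is named. The drug exclusion is "current use of omega-3 PUFA supplements or medications known to affect lipid metabolism", and insulin is not named there or in Table 1.

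Medication is recorded at screening (Table 1, section 3.1) and in a diary for "daily recording of egg consumption, supplement use, and medication intake" (section 3.5). Section 7 analyses longitudinal outcomes by a mixed model with group × time interaction, adjusted for "age, sex, body mass index (BMI), baseline dietary intake, physical activity, baseline clinical parameters, and compliance". Insulin use is not in that list.

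**The concern.** HOMA-IR treats fasting insulin as the body's own response to fasting glucose. In a person who injects insulin, the assay result may also contain the product, and an overnight fast does not remove a long-acting one. An assay that detects the product raises the index. An assay that misses an analogue can lower it, because the person's own secretion may be suppressed. Either way, a higher value no longer means more insulin resistance. Fasting insulin read as a resistance marker has the same defect.

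Insulin resistance is among the markers that the introduction says the trial will investigate, and HOMA-IR is the only calculated index of it. At stake is whether that exploratory result can be interpreted. The triglyceride comparison and the sample size do not depend on it.

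**Working it through.** The plan gives no figure on this point to reproduce. The check sets the passages side by side and then evaluates the plan's own formula. The insulin values, glucose values, share of users and SD ratios below are assumptions, because the documents give none.

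**1. Eligibility against definition.** Treated diabetes qualifies (2.4). Type 1 is excluded; type 2 is not. The drug exclusion covers omega-3 supplements and drugs acting on lipid metabolism. Nothing in 2.4 or Table 1 removes a person with type 2 diabetes for using insulin, and nothing in 5.4 or section 7 treats that person's HOMA-IR differently.

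**2. Sensitivity to measured insulin.** HOMA-IR = G × I ÷ 22.5, with G fasting glucose (mmol/L) and I measured insulin (mU/L):

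| Measured insulin | G = 6.1 | G = 8.0 |
|---|---|---|
| 10 | 2.71 | 3.56 |
| 20 | 5.42 | 7.11 |
| 40 | 10.84 | 14.22 |

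The index is proportional to measured insulin. Doubling the assay result doubles it, whatever the source of the insulin.

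**3. What reaches the between-arm comparison of change.** Write measured insulin as own insulin I plus a detected injected part E. The change from Week 0 to week t is

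(G_t·I_t − G_0·I_0)/22.5 + E_0·(G_t − G_0)/22.5 + G_t·(E_t − E_0)/22.5.

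The first term is the one wanted. If E is stable, the third term is zero and the second is zero when glucose does not move, so most of a stable injected contribution cancels against baseline. If E changes, the third term is pure artefact. Example: at G = 8.0, a rise in measured insulin from 20 to 40 caused only by the injected part moves that person's HOMA-IR by 14.22 − 7.11 = 7.11. One such person in an arm of 60 moves the arm's mean change by 7.11 ÷ 60 = 0.12.

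**4. How many people, and how much noise.** With a share p on insulin, 180p people are affected. If users and non-users have the same mean and the SD in users is k times that in non-users, the overall SD is multiplied by √[(1 − p) + p·k²]:

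| p | Affected of 180 | k = 2 | k = 4 |
|---|---|---|---|
| 2% | about 4 | 1.03 | 1.14 |
| 5% | 9 | 1.07 | 1.32 |
| 10% | 18 | 1.14 | 1.58 |
| 20% | 36 | 1.26 | 2.00 |

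**5. Chance imbalance.** Tables 1 and section 4.1 specify simple randomisation. If 9 users fall at random into three arms, the difference in their number between the two egg arms has variance 9 × (1/3 + 1/3) = 6 and SD 2.45. A difference of three users is 3 ÷ 2.45 = 1.2 SD, so it would not be unusual.

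**The case against.** The strongest reply is that the plan only gives the standard formula with a general remark on direction, and that the analysis population for one exploratory marker belongs in an analysis plan that is not shown. Part of this stands. A reader might infer that the plan orders HOMA-IR to be computed in every participant. It does not say so; this follows only from the absence of a restriction. What remains is that the article fixes a formula and an interpretation that its own eligibility criteria make invalid for some participants, and an analysis plan that follows the article would carry this forward.

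A reader might also infer a sizeable distortion of the treatment comparison. For example, three users at 8 × 60 ÷ 22.5 = 21.33 instead of 3.56 would shift an arm mean of 60 by 3 × (21.33 − 3.56) ÷ 60 = 0.89. That is a purely illustrative single-visit calculation. It assumes the insulin values and a net imbalance of three users. It also leaves out the Week 0 measurement and the group × time model, through which a stable contribution largely cancels. The documents do not support it as an estimate of bias. They do not settle the direction either, since for the assays section 5.4 names only ELISA and other validated methods.

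It would also go too far to say that the metabolic aim rests on HOMA-IR alone. Fasting glucose, HbA1c and C-peptide are measured alongside it. Finally, users may be few. All of this limits the size of the problem; none of it makes the index valid in people who inject insulin.

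**Conclusion.** The point holds as a minor one. Under the stated rule, HOMA-IR and fasting insulin do not measure insulin resistance in insulin-treated type 2 diabetes, which the criteria admit. Randomisation and the baseline measurement remove most systematic bias. What is left is noise, chance imbalance and movement of the index when the insulin dose or its timing changes. The size cannot be fixed from the documents: an assumed share of 2% to 20% and an SD ratio of 2 to 4 give an overall SD between 1.03 and 2.00 times that of non-users. The conclusion rests on at least some enrolled participants using insulin, which the criteria allow but do not guarantee. Section 5.4 classes the outcome as exploratory, and the primary triglyceride analysis and the sample size are unaffected.

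**What to change.** Add to section 5.4:

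- HOMA-IR and fasting insulin are analysed in participants not using exogenous insulin at baseline, identified from the medication record. The number excluded is reported by arm.
- Participants who start insulin after randomisation are not excluded. They stay in the analysis set, their values after initiation are flagged, and a sensitivity analysis examines the influence of those values. Excluding them would select on a post-randomisation event and conflict with the intention-to-treat approach in section 7.
- C-peptide is reported as a supportive marker for all participants. It should not simply replace the index, because injected insulin can itself suppress C-peptide.

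The cost is a few sentences and a slightly smaller sample for HOMA-IR and fasting insulin. C-peptide and medication data are already collected, and eligibility, treatment and sampling do not change.
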